#### Aim 2: Intervention Cohort (n=25)

An additional 25 infants with SCD under 9 months of age will be recruited for the SCCCD intervention following the same inclusion and exclusion criteria as aim 1. Following the 9-month baseline evaluation, consenting families will participate in the 12-month SCCCD program.

#### Aim 3: Qualitative Interview Sample (n=35)

Up to 35 caregivers of children with SCD will be invited to participate in a semistructured interview. Participants will be drawn from three groups: caregivers who completed 6 or more SCCCD intervention visits, caregivers who completed fewer than 6 visits, and caregivers who declined the intervention. With the consent of the primary caregiver, additional caregivers may also be invited to participate. Recruitment will continue until thematic saturation is reached [35].

### Procedures

Developmental evaluations will be conducted at 9, 18, and 30 months of age (±1 month) for children enrolled in both aim 1 and aim 2. Evaluations will take place in a dedicated child-friendly testing room on the Washington University School of Medicine campus, which has a padded floor, child-safe furniture, and space for caregivers to sit comfortably. Five accessible parking spots are reserved directly in front of the testing room, and the space is located within a 5-minute walk of public transportation. Visits will last approximately 60 to 90 minutes. Snacks will be provided to support child engagement during the evaluation, and caregivers will be compensated for their time and travel at each visit. Following institutional review board (IRB) amendment, evaluations may also be conducted in the family’s home for participants residing within the Greater St. Louis Metro area, in response to caregiver feedback regarding barriers to on-site attendance. Any changes are communicated to participants and shared with our community advisory board.

Demographic information and caregiver surveys will be collected using REDCap, a HIPAA-secure web-based data capture system, administered on a research tablet [36,37]. Survey data may also be completed by caregivers remotely via a secure web-link before or after the visit to reduce in-person visit burden. Assessors will be trained to maintain adherence to the evaluation protocol prior to data collection. Following each evaluation, the assessor will prepare a written summary report of the child’s developmental scores, review the results with the caregiver, and share the report with the child’s pediatrician and hematologist at the family’s request. If a developmental delay is identified (>1 SD below the mean), the research team will discuss the results with the caregiver and offer a referral to Early Intervention services, the federally funded, state-administered early intervention program available to eligible children under 3 years of age at no cost to families [38,39].

Retention strategies include SMS text message reminders prior to each scheduled visit; flexible scheduling, including early morning, evening, and weekend appointments; and reimbursement for parking or public transportation. Text message reminders have been effective in reducing visit cancelations in our prior work [20].

For aim 2, a pediatric occupational therapist with training in the PAT curriculum will conduct 12 monthly home visits with each enrolled family following the 9-month baseline evaluation. Visit scheduling will allow for up to 15 to 18 months of delivery to accommodate missed visits and ensure all families receive equivalent intervention dosage. Visits will be documented using daily notes that capture completed activities, caregiver engagement, visit duration, and any SCD-related topics reviewed.

For aim 3, semistructured interviews will be conducted with up to 35 caregivers of children enrolled in aim 2. Interviews will be conducted by the method of the participant’s choosing (eg, phone, HIPAA-secure video call, or in person) and are expected to last approximately 30 to 45 minutes. Interviews will be audio-recorded and transcribed verbatim. Two research team members will review all transcripts for accuracy prior to analysis. Caregivers will be compensated for their time.

All data will be stored with 2 levels of password protection. Paper consent documents will be maintained in a locked cabinet in a locked office. Data will be accessible only to the research team.

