### Measures

All outcome measures are summarized in Table 1. Demographic information will be collected from all participants at enrollment, including caregiver age, education, health literacy, marital status, household income, racial or ethnic identity, and number of children in the household. Clinical information collected for children with SCD will include SCD genotype, insurance status, hospitalizations and treatments, disease-modifying medication use, and neuroimaging results if available.

**Table 1. T1:** Summary of outcome measures.

Measure	Purpose	Type	Time point (months)	Aim
Bayley-4^a^	Child development	Clinician administered	9, 18, and 30	1 and 2
ASQ-3^b^	Child development	Caregiver report	9, 18, and 30	1 and 2
ITACS^c^	Child participation in family routines	Caregiver report	9, 18, and 30	1 and 2
BRIEF-P^d^	Executive functioning	Caregiver report	30 only	1 and 2
HOME^e^ Inventory	Home environment	Clinician observation	9, 18, and 30	2
PROMIS^f^ Depression (8 items)	Caregiver mental health	Caregiver report	9, 18, and 30	1 and 2
Semistructured interview	Implementation determinants	Interview	Ongoing	3

a Bayley-4: Bayley Scales of Infant Development, Fourth Edition.

b ASQ-3: Ages and Stages Questionnaires, Third Edition.

c ITACS: Infant Toddler Activity Card Sort.

d BRIEF-P: Behavior Rating Inventory of Executive Function-Preschool.

e HOME: Infant Toddler Home Observation for Measurement of the Environment.

f PROMIS: Patient-Reported Outcomes Measurement Information System.

The Bayley Scales of Infant Development, Fourth Edition (Bayley-4) is the primary outcome measure and has been the gold standard for evaluating and identifying developmental delay in children for over 50 years [25]. The Bayley-4 is completed in 45 to 60 minutes and evaluates 5 developmental domains: cognition, fine motor, gross motor, receptive language, and expressive language. Raw scores are converted to scaled scores, where a score of 10 indicates performance at the 50th percentile. A score greater than 1 SD below the mean will be classified as a developmental delay.

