The Ages and Stages Questionnaire, Third Edition (ASQ-3) is a caregiver report screener used widely in primary care and research settings that assesses development across the domains of communication, gross motor, fine motor, problem solving, and personal-social skills in approximately 10 minutes [10,40]. While the ASQ-3 is time- and cost-efficient, it is insufficiently detailed to identify early indicators of mild-to-moderate developmental delays when used alone [5,10,18,20,41,42].

The Survey of Well-Being of Young Children (SWYC) is a brief, validated caregiver report screener that captures developmental and behavioral milestones as well as family context factors including caregiver depression and social determinants of health [43,44]. The SWYC was added to the protocol following community partner and community advisory board input to capture additional environmental and contextual factors and to allow comparison with other commonly used screening measures.

The Infant Toddler Activity Card Sort (ITACS) is a picture-based caregiver report tool developed and validated by members of this team to identify concerns related to child participation in family activities and routines [33,34,45]. Caregivers are presented with photographs depicting common infant and toddler activities and asked to identify those that present a challenge for their child.

The Behavior Rating Inventory of Executive Function-Preschool (BRIEF-P) is a widely used caregiver report measure of executive functioning for children as young as 2 years of age, designed to identify how a child functions within the context of their individual environments [46]. The BRIEF-P will be administered at the 30-month time point only.

The Infant Toddler Home Observation for Measurement of the Environment Inventory [9] is a 42-item checklist completed by a research team member that evaluates the quality and quantity of stimulation and support available to the child in the home environment [47]. The HOME (Infant Toddler Home Observation for Measurement of the Environment) will be administered at all 3 time points for children enrolled in aim 2.

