### Data Analysis

#### Aim 1

Evaluations will be scored according to their respective manuals. Mixed effects regression will be used to analyze developmental outcome data, with time, group, and time-by-group interaction entered as fixed effects. This approach accounts for within-subject and within-group variability across the 3 longitudinal time points. Scores from the Bayley-4 will be compared to the ASQ-3. Covariates will include race, age, sex, caregiver education, socioeconomic status, disease-modifying medication use, and therapeutic intervention received. The number of evaluations completed and any therapeutic or behavioral interventions received (eg, physical therapy, OT, speech-language therapy) will be documented. Children who receive therapy services during the study period will be analyzed separately.

#### Aim 2

Standardized scores will be calculated for each assessment according to the respective manuals. Scores greater than 1 SD below the mean will be classified as a developmental delay. Repeated measures ANOVA will be used to compare group mean scores at 9, 18, and 30 months. Logistic regression will compare the number of children classified with a delay at 30 months to the aim 1 cohort. The number of caregivers approached and enrolled will be documented, and visits scheduled and completed, along with topics from visit notes, will be summarized. Additional analyses will examine possible changes in the home environment and caregiver mental health before and after the intervention. When the outcome is binary, a mixed effects logistic regression will be used, with time, group, and time-by-group interaction entered as fixed effects and variation of subject intercept as a random effect. Time will also be tested as a random effect in a more elaborate model.

#### Aim 3

Two research team members will use an iterative inductive and deductive thematic analysis approach to review all transcripts and generate themes for a preliminary codebook [60]. The preliminary codes will be applied to 4 interviews using NVivo software; any deviations will be discussed, and the revised codebook will be applied to all remaining interviews [62]. Codes will be analyzed for themes, and participation data from aim 2 will be summarized and integrated with qualitative findings [63,64].

The study protocol and deidentified data will be made available from the corresponding author on request and consistent with the NIH Data Management and Sharing Plan.

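### Caregiver surveys, including the ASQ-3 that is compared with the Bayley-4, may be completed after the visit and so possibly after the caregiver has been told the Bayley-4 result

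*Protocol article*

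**What the plan says.** All of the following is in the protocol article.

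- **Survey timing (Procedures).** Surveys are administered on a research tablet, with a remote option: "Survey data may also be completed by caregivers remotely via a secure web-link before or after the visit". The stated reason is to lighten the visit.
- **Feedback (Procedures, same paragraph).** Following each evaluation, "the assessor will prepare a written summary report of the child’s developmental scores, review the results with the caregiver". If a delay is found, "the research team will discuss the results with the caregiver and offer a referral to Early Intervention services". No date or interval is given for either conversation.
- **Instruments (Measures).** Table 1 lists the ASQ-3, ITACS, BRIEF-P and PROMIS Depression as "Caregiver report". The text says that the ASQ-3 "is a caregiver report screener used widely in primary care and research settings", and it describes the SWYC as a caregiver-report screener too. The Bayley-4 is clinician administered and is the primary outcome measure.
- **Analysis (Data Analysis).** Under aim 1, "Scores from the Bayley-4 will be compared to the ASQ-3", with no condition on which was completed first. Under aim 2, caregiver mental health is examined before and after the intervention.
- **Limitations.** Response bias in caregiver report is acknowledged in general terms. Knowledge of the Bayley-4 result is not mentioned.

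**The concern.** When a screener is compared with a reference test, the screener should be answered without knowledge of the reference result. A caregiver who has just gone through the child's Bayley-4 scores, perhaps with a referral offered, is no longer an independent informant about the same skills. Caregivers told of a delay may report more problems, and those who were reassured may report fewer. Both movements bring the ASQ-3 closer to the Bayley-4.

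The comparison matters to this study. The Measures section holds that the ASQ-3 alone is not detailed enough to pick up milder delays, and inflated agreement would hide that weakness. The SWYC was added partly so that it could be compared with other screening measures, and it is exposed in the same way.

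The aim 2 mental health analysis is exposed through its baseline. The Ethical Considerations section accepts that talking about development may cause a caregiver mild stress or anxiety. If the 9-month PROMIS form follows news of a delay, it may be raised for a time, and a later fall could be read as an effect of the intervention.

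**Working it through.** The article gives no figure to reproduce, so the check is mainly one of sequence.

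**1. Can a survey come after the visit?** Yes. The Procedures section permits it in terms.

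**2. Is the result disclosed to the caregiver?** Yes, following every evaluation, with a further discussion when the score indicates a delay.

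**3. Could disclosure come before a post-visit survey?** The article says that "Visits will last approximately 60 to 90 minutes", and the Measures section gives 45 to 60 minutes for the Bayley-4. The time left in the visit is therefore:
- shortest: 60 − 60 = 0 minutes
- longest: 90 − 45 = 45 minutes

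Same-day scoring and review is possible but not established. If the review takes place days later, a survey completed soon after the visit would still precede it. The text permits the unwanted order but does not make it certain.

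**4. Is the ASQ-3 among the surveys concerned?** The article does not list which instruments go by web-link. The ASQ-3 is included because it is a caregiver-report form. For the picture-based ITACS, remote completion is a weaker inference.

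**5. Does any rule in the analysis deal with the order?** No. The comparison is not limited to forms completed before the results review.

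**6. Can the size be derived?** Let s be the true ASQ-3 sensitivity against a Bayley-4 delay, f the share of forms completed after feedback, and q the share of otherwise missed children whom an informed caregiver would then report as having a problem. Then

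apparent sensitivity = s + f × q × (1 − s).

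The article gives none of s, f and q. With f and q each free between 0 and 1, the inflation runs from 0 to 1 − s, the whole possible range. The direction is reasonably clear; the amount is not.

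**7. How much data can still be protected?** For aim 1, 24 + 26 = 50 of 100 children are still to be recruited; for aim 2, 20 of 25. If the rows of Table 4 count evaluations done at each age, aim 1 has (12 + 22 + 18) + (10 + 15 + 16) = 52 + 41 = 93 so far and aim 2 has 5. That is the most for which the order would have to be checked in retrospect.

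**The case against.** The strongest reply is that this is a condensed article. Tablet completion comes first and the web-link is an added option. Assessors are trained to an evaluation protocol that is not reproduced, and that document may put surveys before feedback. This stands as a caution: the study may have such a rule. It does not dispose of the point, because the article does not merely leave the order out. It states a timing rule, and that rule allows either order. An analysis plan could later exclude late forms but could not make them independent again.

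It can also be said that inflated agreement works against the authors' own view of the ASQ-3, so for that view the bias is conservative. That is correct, but the estimate would still be biased.

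Full independence is not attainable in any case. Caregivers can sit in the testing room, and feedback at 9 and 18 months can colour later reports. Both points stand. Ordering within a visit removes only the most direct route.

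A reader might infer more than the article supports:

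- **That post-visit forms are always completed with knowledge of the result.** The date of the review is not given.
- **That the incidence of delay is biased.** Delay is classified from standardized scores, and the primary outcome, the Bayley-4, is clinician administered.
- **That ASQ-3 sensitivity is overstated by some number of points.** Every input would be assumed, and the article does not name a sensitivity estimate.
- **That aim 1 would show a spurious cohort difference in caregiver mood or child participation.** The aim 1 analysis does not specifically name a PROMIS or ITACS group comparison.

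**Conclusion.** The point holds as a weakness in the stated procedure. Caregiver forms may be completed after the caregiver knows the Bayley-4 result, and the planned Bayley-4/ASQ-3 comparison does not allow for it. The likely effect is inflated agreement in that comparison, together with a possible shift in the 9-month PROMIS baseline for aim 2. The primary outcome is untouched.

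The conclusion assumes that the ASQ-3 and PROMIS are among the forms that may be completed remotely, that at least some are completed after the review, and that knowing the result moves answers towards it. Forms completed before the review are unaffected. The size cannot be stated. The change is worth making because it is cheap and half of aim 1 is still to be recruited.

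**What to change.** **Procedures.** Replace the permission to complete surveys at any time around the visit with: before the visit, or after it but before Bayley-4 results are reviewed with the caregiver. Record the date and time of the results review. REDCap survey time stamps alone cannot show that a form was late, and the article does not say that the review time is recorded.

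**Unfinished forms.** Do not hold back feedback or referral for them. Accept the form when it arrives and flag it as completed after feedback.

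**Data Analysis.** Base the Bayley-4 versus ASQ-3 comparison on forms completed before feedback, and add the late forms in a sensitivity analysis. For data already collected, do this where the feedback date can be established, and report how many forms could not be classified.

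**Cost.** One changed sentence in Procedures, one recorded time per evaluation and one line in the analysis. Remote completion stays available, which matters for burden in a study with 13 withdrawals among 72 consents. A few forms will leave the main comparison. Feedback from earlier visits can still influence later reports and should be named as a limitation.

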### Measures

All outcome measures are summarized in Table 1. Demographic information will be collected from all participants at enrollment, including caregiver age, education, health literacy, marital status, household income, racial or ethnic identity, and number of children in the household. Clinical information collected for children with SCD will include SCD genotype, insurance status, hospitalizations and treatments, disease-modifying medication use, and neuroimaging results if available.

**Table 1. T1:** Summary of outcome measures.

Measure	Purpose	Type	Time point (months)	Aim
Bayley-4^a^	Child development	Clinician administered	9, 18, and 30	1 and 2
ASQ-3^b^	Child development	Caregiver report	9, 18, and 30	1 and 2
ITACS^c^	Child participation in family routines	Caregiver report	9, 18, and 30	1 and 2
BRIEF-P^d^	Executive functioning	Caregiver report	30 only	1 and 2
HOME^e^ Inventory	Home environment	Clinician observation	9, 18, and 30	2
PROMIS^f^ Depression (8 items)	Caregiver mental health	Caregiver report	9, 18, and 30	1 and 2
Semistructured interview	Implementation determinants	Interview	Ongoing	3

a Bayley-4: Bayley Scales of Infant Development, Fourth Edition.

b ASQ-3: Ages and Stages Questionnaires, Third Edition.

c ITACS: Infant Toddler Activity Card Sort.

d BRIEF-P: Behavior Rating Inventory of Executive Function-Preschool.

e HOME: Infant Toddler Home Observation for Measurement of the Environment.

f PROMIS: Patient-Reported Outcomes Measurement Information System.

The Bayley Scales of Infant Development, Fourth Edition (Bayley-4) is the primary outcome measure and has been the gold standard for evaluating and identifying developmental delay in children for over 50 years [25]. The Bayley-4 is completed in 45 to 60 minutes and evaluates 5 developmental domains: cognition, fine motor, gross motor, receptive language, and expressive language. Raw scores are converted to scaled scores, where a score of 10 indicates performance at the 50th percentile. A score greater than 1 SD below the mean will be classified as a developmental delay.

The Ages and Stages Questionnaire, Third Edition (ASQ-3) is a caregiver report screener used widely in primary care and research settings that assesses development across the domains of communication, gross motor, fine motor, problem solving, and personal-social skills in approximately 10 minutes [10,40]. While the ASQ-3 is time- and cost-efficient, it is insufficiently detailed to identify early indicators of mild-to-moderate developmental delays when used alone [5,10,18,20,41,42].

The Survey of Well-Being of Young Children (SWYC) is a brief, validated caregiver report screener that captures developmental and behavioral milestones as well as family context factors including caregiver depression and social determinants of health [43,44]. The SWYC was added to the protocol following community partner and community advisory board input to capture additional environmental and contextual factors and to allow comparison with other commonly used screening measures.

The Infant Toddler Activity Card Sort (ITACS) is a picture-based caregiver report tool developed and validated by members of this team to identify concerns related to child participation in family activities and routines [33,34,45]. Caregivers are presented with photographs depicting common infant and toddler activities and asked to identify those that present a challenge for their child.

The Behavior Rating Inventory of Executive Function-Preschool (BRIEF-P) is a widely used caregiver report measure of executive functioning for children as young as 2 years of age, designed to identify how a child functions within the context of their individual environments [46]. The BRIEF-P will be administered at the 30-month time point only.

The Infant Toddler Home Observation for Measurement of the Environment Inventory [9] is a 42-item checklist completed by a research team member that evaluates the quality and quantity of stimulation and support available to the child in the home environment [47]. The HOME (Infant Toddler Home Observation for Measurement of the Environment) will be administered at all 3 time points for children enrolled in aim 2.

The Patient-Reported Outcomes Measurement Information System (PROMIS) Depression Short Form (8 items) will be completed by caregivers at each time point to assess caregiver mental health, given the established association between caregiver depression and child developmental outcomes [16,48,49]. Caregivers with concerning scores on the PROMIS Depression screener, based on prespecified cutoffs, will be referred to behavioral health services.

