### Participants

#### Aim 1: Incidence Cohort (n=100)

Children with SCD (n=50) under 9 months of age with all SCD genotypes and their caregivers will be recruited from the Sickle Cell Clinic at SLCH. Children without SCD (n=50) will be recruited as a comparison cohort and matched at the group level to the SCD cohort on the distributions of age, sex, race, socioeconomic status, and Area Deprivation Index [32], rather than paired individually. Group-level matching will be finalized after enrollment. Typically developing children will be recruited through SLCH general medicine, community early childhood centers, local pediatricians, public libraries, local early intervention providers, and faith-based organizations, using methods previously successful in this lab [33,34]. Children will be excluded if they have a diagnosis associated with developmental delay that is not attributable to SCD, or if the family is not English-speaking.

Caregivers of children with SCD will be approached by phone or following a regularly scheduled clinic visit. Interested caregivers will review the informed consent document with a member of the research team by phone, Health Insurance Portability and Accountability Act (HIPAA)–secure video call, or in person.

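### Gestational age at birth is not named among the matching factors, collected variables or Aim 1 covariates, so unequal preterm birth could bias the SCD-versus-peer contrast in either direction

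*Protocol article*

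**What the plan says.** The protocol article sets out its variables in three places.

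- **Collection (Measures).** For all participants, the demographic items named are "caregiver age, education, health literacy, marital status, household income, racial or ethnic identity, and number of children in the household". For clinical data the text is: "Clinical information collected for children with SCD will include SCD genotype, insurance status, hospitalizations and treatments, disease-modifying medication use, and neuroimaging results if available". No clinical list is given for comparison children.
- **Matching (Aim 1: Incidence Cohort).** The comparison cohort is matched at group level on "distributions of age, sex, race, socioeconomic status, and Area Deprivation Index", and matching is finalized after enrollment.
- **Adjustment (Data Analysis, Aim 1).** "Covariates will include race, age, sex, caregiver education, socioeconomic status, disease-modifying medication use, and therapeutic intervention received".

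Visits are set at 9, 18 and 30 months of age, with a window of one month either side (Procedures). The text does not say whether age is chronological or corrected. On the outcome, Measures says: "A score greater than 1 SD below the mean will be classified as a developmental delay". On scoring, Data Analysis says: "Evaluations will be scored according to their respective manuals". Children with a diagnosis linked to developmental delay that is not due to SCD are excluded. Prematurity is not mentioned there, and no gestational-age limit is given.

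**The concern.** Aim 1 is a non-randomized comparison of age-normed infant scores, so any cause of low early scores that is unevenly spread between the cohorts becomes part of the SCD-versus-peer contrast. Preterm birth is an obvious candidate, and it is absent from every list the article gives. The model as written would leave it unadjusted.

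Balance cannot be taken for granted. Children with SCD come from one specialist clinic. Comparison children come from general medicine, community centers, pediatricians, libraries, early intervention providers and faith-based organizations. In Table 3, 25 of 26 children with SCD are Black or African American against 7 of 24 comparison children. The most deprived Area Deprivation Index band holds 14 of 26 against 4 of 23 with a value.

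The group difference and the time-by-group term are both at stake. The Introduction says delays may worsen with age and that this trajectory has not been rigorously evaluated. Aim 2 inherits the problem, because its 30-month delay count is compared with the Aim 1 cohort without randomization. An analysis plan can adjust only for what was recorded in both groups, so collection has to be settled now.

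**Working it through.** The article states no figure on this point, so there is none to reproduce. The check has two parts: the text, then an illustration of size.

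**1. The lists.** Gestational age, prematurity, birth weight and corrected age appear nowhere in the article: not in the demographic items, the SCD-only clinical items, the five matching factors, the exclusions or the seven named covariates.

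**2. Bias in the mean.** Inputs, all assumed because the article gives none: an imbalance in preterm share of Δp = 0.10; a deficit in preterm children of 1 to 3 scaled points; a scaled-score SD of 3 (the article gives only the mean of 10).

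- Bias = Δp × deficit = 0.10 × 1 to 0.10 × 3 = 0.1 to 0.3 points.
- In SD units: 0.1/3 to 0.3/3 = 0.03 to 0.10 SD.

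**3. Bias in the delay rate, one domain.** More than 1 SD below the mean is a score of 6 or lower. With a continuity correction, P(delay) = Φ((6.5 − mean)/3).

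| Mean | P(delay) | Increase over mean 10 | × 0.10 |
|---|---|---|---|
| 10 | 12.2% | – | – |
| 9 | 20.2% | 8.1 points | 0.8 points |
| 8 | 30.9% | 18.7 points | 1.9 points |
| 7 | 43.4% | 31.2 points | 3.1 points |

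**4. Scale against the design.** With 50 per group, one time point and no adjustment, SE = √(2/50) = 0.20 SD. The difference detectable with 80% power at two-sided 5% is (1.960 + 0.842) × 0.20 = 0.56 SD. A bias of 0.03 to 0.10 SD raises the false-positive rate from 5% to between 5.3% and 7.9%.

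**5. Wider range.** Let the imbalance run from 5 to 20 percentage points and the deficit from 0.3 to 1.0 SD, with the cut at exactly 1 SD (15.9% below it). The bias is then 0.05 × 0.3 = 0.015 SD to 0.20 × 1.0 = 0.20 SD. The delay rate shifts by 0.4 to 6.8 percentage points, and the false-positive rate is 5.1% to 17.0%. For an imbalance of zero, all of these biases are zero.

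**6. Trajectory, only if scores are not age-corrected.** Birth 8 weeks early is 8/4.345 = 1.84 months. As a share of age:

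- 9 months: 1.84/9 = 20.5%
- 18 months: 1.84/18 = 10.2%
- 30 months: 1.84/30 = 6.1%

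The effect would fade across visits and so load on the time-by-group term. If preterm births were more common in the SCD group, the deficit would look largest at 9 months and then shrink. That would resemble catch-up and could mask the worsening suggested in the Introduction. An excess among comparison children would act the other way.

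**7. Aim 2.** With 25 children, each one reclassified moves the 30-month delay rate by 1/25 = 4 percentage points.

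**The case against.** Four objections carry weight.

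- **Open lists.** The collection and covariate lists are worded as non-exhaustive, and this is a condensed article. A reader might infer that gestational age is not collected. The documents do not show that; it may sit on a case report form. Only the matching list reads as closed, and adjustment can stand in for matching. This objection stands, which is why the fix allows for confirmation.
- **Scoring by the manuals.** A reader might infer that delay is classified on uncorrected age and that the trajectory is therefore distorted. The article does not say so, because it defers to manuals that are not at hand. Step 6 is conditional on no correction. Correction would itself require gestational age, however, and it would not remove a remaining difference between cohorts in preterm birth.
- **Partial safeguards.** The exclusion may remove some affected preterm children. Adjusting for race and socioeconomic status may absorb part of any imbalance that follows them. Table 3 is interim, and matching is not yet final. These points reduce the likely bias but do not make it checkable.
- **Size and direction.** A reader might infer that prematurity would pass as an SCD deficit. With no preterm rates in the article, the direction is unknown. Recruiting comparison children through early intervention providers could reverse it. The central range is also small next to the 0.56 SD that the design can detect.

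**Conclusion.** The point holds as a worthwhile, inexpensive improvement, not as proof of a biased result. Followed as written, the Aim 1 model does not adjust for preterm birth, and the article describes no clinical data for comparison children from which it could be examined. The bias is about 0.03 to 0.10 SD, or 0.8 to 3.1 percentage points of delay rate in one domain. This rests on an assumed 10-point imbalance, a deficit of 1 to 3 scaled points and an SD of 3. It is zero if the cohorts are balanced, and its sign is unknown. The effect on the time-by-group term arises only if scores are not age-corrected. The documents establish neither non-collection nor a distorted trajectory.

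**What to change.** - Record gestational age at birth for both Aim 1 cohorts and Aim 2, or confirm that it is already recorded. For children already enrolled, obtain it by caregiver report or from the record.
- State one age rule for scoring, consistent with the manuals, and apply it to every child at every visit.
- Report gestational age by group.
- Add it as a covariate in the Aim 1 model and in the Aim 2 contrast, with a sensitivity analysis restricted to term-born children.

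The cost is one item on an existing REDCap form, a call-back to enrolled families, some recall error in the retrospective entries, and one more covariate in a small sample. The timing is good: by the article's own count, 50 children remain to be recruited for Aim 1 and 20 for Aim 2.
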